## Abstract

**Background:**

Despite significant advancements in obstetric care, the incidence of preeclampsia remains a substantial public health challenge, and effective strategies to prevent the disease progression remain limited, particularly in low-resource settings. N-acetylcysteine (NAC), an antioxidant and glutathione precursor, has demonstrated anti-inflammatory and vasodilatory effects, making it a promising candidate for repurposing. However, robust evidence from well-powered randomized controlled trials is lacking.

**Objective:**

This study will evaluate the impact of NAC on the time-to-disease progression in pregnant women with early-onset preeclampsia in Lagos, Nigeria.

**Methods:**

This is the study protocol for a proof-of-concept, double-blind, randomized, controlled trial to be conducted between April 2026 to July 2028 at the maternity units of the two teaching hospitals in Lagos, Nigeria. At baseline, n = 153 sexually active women aged 18 years or older diagnosed with early-onset preeclampsia at 24–34 weeks’ gestation will be randomised to receive either daily oral tablet containing 600 mg of NAC or a placebo tablet that is matched for appearance and the dosing regimen in addition to standard antenatal care from diagnosis (randomisation) until either 34 weeks’ gestation or delivery, whichever comes first. The primary endpoint is the time-to-progression (in days) of early-onset preeclampsia to severe disease. The data analysis will be conducted on an intention-to-treat basis. Kaplan-Meier estimates with a Log-rank test will be used to calculate and compare the time-to-disease progression for the treatment groups, while Cox proportional hazard models with a backwards conditional method will be used to compare the primary endpoint between the treatment arms while adjusting for other covariates for precision using hazard ratios (HRs) and 95% confidence intervals (95%CIs). Subgroup analyses will also be performed to assess the differential effects of significant covariates on the impact of NAC on disease progression. Statistical significance will be reported as *P* < 0.05.

**Discussion:**

This study will evaluate the efficacy of daily oral NAC compared to placebo in treating pregnant women with early-onset preeclampsia. If proven effective, NAC could offer a safe, affordable, and scalable intervention to reduce the burden of preeclampsia, particularly in resource-constrained settings.

## Introduction

Preeclampsia is a progressive multisystemic complication of pregnancy characterized by hypertension and often proteinuria, typically occurring after 20 weeks of gestation [1]. It affects approximately 2–8% of pregnancies globally [2] and up to 16.7% among pregnant women in Nigeria [3]. Preeclampsia remains a leading cause of maternal and perinatal morbidity and mortality worldwide, particularly in low- and middle-income countries [4]. Preeclampsia with severe features represents an escalation of preeclampsia severity and is associated with a higher risk of adverse maternal and fetal outcomes [2,5]. Severe features of preeclampsia include a systolic blood pressure of at least 160 mmHg or a diastolic blood pressure of at least 110 mmHg, thrombocytopenia, impaired liver function, severe persistent right upper quadrant pain, progressive renal insufficiency, pulmonary oedema, and new-onset cerebral or visual disturbances [6].

Despite significant advancements in obstetric care, the incidence of preeclampsia remains a substantial public health challenge [7] and effective strategies to prevent the disease progression remain limited, particularly in low-resource settings. While certain interventions, such as low-dose aspirin prophylaxis [8] in high-risk women, have shown some efficacy in reducing the risk of preeclampsia, there remains a need for additional measures to prevent the development of severe disease in women with early-onset preeclampsia, particularly in resource-constrained settings where the burden of disease is greatest [4]. Currently, the only cure for preeclampsia is delivery of the fetus and placenta [7,9] however, this is commonly associated with iatrogenic preterm delivery. To prevent this complication and improve maternal and perinatal outcomes, research efforts are currently focused not only on the prevention of preeclampsia but also on its treatment and prevention of its severe features.

The pathophysiology of preeclampsia is complex and not completely understood, but it is widely recognized that oxidative stress and inflammation play crucial roles in its development and progression [10]. N-acetylcysteine (NAC), a precursor to the antioxidant glutathione, has shown promise in reducing oxidative stress and inflammation [11]. The potential benefits of NAC extend beyond its antioxidant properties; it has also demonstrated anti-inflammatory and vasodilatory effects, making it a potential therapeutic agent for conditions characterized by oxidative stress and endothelial dysfunction, such as preeclampsia [11]. Recent preclinical and preliminary clinical studies [12–15] have suggested that NAC could mitigate the oxidative stress associated with preeclampsia, thereby reducing the progression to severe disease. However, despite the established long-standing safety profile of NAC in both general and obstetric populations [16–21], especially as an antidote for acetaminophen poisoning and as a mucolytic agent. There is a significant gap in the literature regarding definitive evidence of its efficacy in reducing the progression of preeclampsia in well-powered, randomised, controlled trials among women with early-onset preeclamptic pregnancies.

Our proposed proof-of-concept randomized controlled trial aims to address this knowledge gap by providing more robust data on the potential benefits of NAC in this context, evaluating its impact on the time-to-disease progression in pregnant women with early-onset preeclampsia in Lagos, Nigeria. The central hypothesis of the study is that NAC can be repurposed as an effective therapy to prolong disease progression in early-onset preeclamptic pregnant women. If proven effective in this context, NAC could provide a low-risk, affordable, and accessible intervention to reduce the burden of preeclampsia, which remains a significant cause of maternal and perinatal morbidity and mortality, particularly in low-resource settings.

## Patients and methods

### Study design and setting

This is a proof-of-concept, multicenter, randomized, double-blind, placebo-controlled, superiority trial that will be conducted in the maternity units of two hospitals in Lagos, Nigeria, between April 2026 and July 2028. The hospitals, Lagos University Teaching Hospital (LUTH) in Idi-Araba and Lagos Island Maternity Hospital (LIMH) on Lagos Island, are two of the foremost public health institutions in Lagos State, southwest Nigeria, offering care to a population of over 20 million inhabitants [22]. These hospitals have established obstetrics departments with well-equipped and functional maternal units and jointly managed up to 1,787 cases of preeclampsia/eclampsia in 2024.

### Study population and eligibility criteria

Potentially eligible ‌‌women in the two study sites are those aged 18 years or older diagnosed with early-onset preeclampsia at 24–34 weeks’ gestation [23]. Preeclampsia is defined as new-onset hypertension, characterised by systolic blood pressure of ≥140 mmHg or diastolic blood pressure of ≥90 mmHg, measured with an appropriately sized cuff at least 4–6 hours apart, and accompanied by proteinuria, defined as ≥300 mg in a 24-hour urine collection or ≥100 mg/L (equivalent to ≥2+ on dipstick urinalysis) in at least two random urine samples taken 4–6 hours apart after 20 weeks of gestation [2] and with no evidence of end-organ dysfunction. The exclusion criteria are women unwilling to provide informed consent, those with known allergy or hypersensitivity to NAC or any of its components, current use of medications or supplements that could interfere with the effects of NAC, such as other antioxidants, nitro-glycerine, activated charcoal, and chloroquine, receipt of a long course of mineral supplements containing NAC during the 6 months before enrolment, bleeding disorders, bronchial asthma, history of alcohol or drug abuse, active liver disease, significant chronic renal impairment, or major fetal anomalies, and women with preeclampsia with severe features or eclampsia at the time of randomisation.

### Study outcomes

The primary outcome measure was time-to-disease progression (in days) among women with early-onset preeclampsia, defined as the interval from diagnosis to the first occurrence of a composite endpoint indicating clinical deterioration. Disease progression is defined as the development of any of the following: consistently elevated blood pressure of 160/110 mmHg or higher; severe proteinuria of 3+ or a urine protein/creatinine ratio of 0.3 or higher; platelet counts less than 100,000/µL; elevated liver enzymes (AST/ALT) or evidence of hepatic dysfunction; serum creatinine level greater than 1.1 mg/dL or doubling of baseline creatinine in the absence of other renal diseases; symptoms and signs of pulmonary oedema such as dyspnoea and crackles on lung auscultation; cerebral or visual disturbances such as headaches, visual disturbances, altered mental status, seizures (eclampsia), or other neurological symptoms; and evidence of placental dysfunction such as placental abruption, fetal growth restriction or oligohydramnios on ultrasound examination [2,5]. Participants who do not experience disease progression will be censored at delivery or at the end of follow-up. Secondary outcomes will include (1) safety and treatment tolerability, (2) maternal outcome (maternal mortality), and (3) composite neonatal outcomes, including low birth weight in term neonates (baby’s birth weight less than 2500g), IUGR, stillbirth, NICU admission, and perinatal and neonatal mortality. Women who develop preeclampsia with severe features will be managed as per the obstetric unit protocol and will be excluded from further participation in the study.

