### Study procedures

The study team will screen and enrol n = 153 consecutively consenting pregnant women diagnosed with early-onset preeclampsia during their routine antenatal care or at the maternity units of the participating hospitals. We will enrol approximately 40% of participants at LUTH (n = 61) and 60% at LIMH (n = 92), reflecting differences in patient volume and prior recruitment performance. Once the study intent and procedures are introduced and informed consent obtained, baseline sociodemographic, obstetric, dietary, and laboratory (haemoglobin, liver function tests, kidney function tests, glutathione, and homocysteine status) information will be collected using an electronic case report form (CRF) on REDCap. A baseline ultrasound scan assessment will be done and documented. Gestational age is based on the date of the participant’s last menstrual period, which will be obtained at the time of random assignment or calculated from the baseline ultrasound biometry. Body mass index (BMI) is obtained by dividing the actual maternal weight (calculated by subtracting the estimated fetal weight at enrolment using a normogram chart from the measured maternal weight) by the maternal height (in kg/m^2^).

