### Randomization and allocation concealment

Participants will be randomly assigned using a 1:1 block random sequence of 4–6 blocks generated by the study statistician from Random Allocation software version 1.0 (May 2004) prepared in advance of the trial to receive either a daily oral tablet containing 600 mg of NAC or a placebo tablet to match the NAC tablets in size, shape, colour, and overall appearance to maintain blinding in addition to standard antenatal care from diagnosis (randomisation) until either 34 weeks’ gestation or delivery, whichever comes first [Fig 1]. The active drug (NAC) and placebo tablets will be packed in identical, coded, transparent dispensing sachets by the onsite pharmacy technician. The technician will then store the coded randomisation list in a sealed, opaque envelope, which will be kept in a locked file cabinet at the study site until the end of the study. The 600 mg oral daily dosage of NAC was selected after a careful review of the literature on the effectiveness of NAC in exerting antioxidant, anti-inflammatory, and antiproliferative effects while maintaining a favourable safety profile [16–21]. Furthermore, a low dose of 600 mg daily aligns with widely available commercial formulations that offer better gastrointestinal tolerability, which is important for sustained adherence in our study population and will also simplify procurement and ensure consistent dosing during the study. The placebo tablets will be composed of inert excipients, including microcrystalline cellulose, lactose, and magnesium stearate, and will contain no active pharmacological ingredient. Given the characteristic sulfur-like odour and taste of NAC, both NAC and placebo tablets will be administered with Coca-Cola Zero Sugar immediately prior to ingestion to mask any sensory differences and minimize the risk of unblinding. Participants, investigators, and outcome assessors will remain blinded to treatment allocation throughout the study period. To evaluate the effectiveness of blinding, a blinding assessment will be conducted at the end of the intervention period. Participants and study personnel will be asked to indicate their perceived treatment allocation (NAC, placebo, or unsure). The success of blinding will be assessed by comparing the distribution of guesses between groups against that expected by chance. All study participants, irrespective of treatment arm allocation, will receive standard-of-care management for early-onset preeclampsia in accordance with the institutional protocol and internationally accepted guidelines. The study intervention will only be administered as an adjunct to standard care, which will include corticosteroids for fetal lung maturation, antihypertensive treatment, magnesium sulphate for seizure prophylaxis (when indicated), close maternal and fetal monitoring, and delivery based on standard clinical indications.

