
**Fig 1 pone.0347695.g001:**
[figure not shown]
Trial flow chart.

**Follow-up evaluations:** Data collection will commence on the day the participant is randomized into the trial and will continue until the trial is terminated or the participant withdraws from the trial at any time for any reason. Study visits will be scheduled every two weeks until 32 weeks and weekly thereafter until delivery [Table 1]. Participants will be monitored using a daily symptom diary to record features of severity—headaches, visual disturbances (e.g., blurred vision, scotoma), dyspnoea, and right hypochondria or epigastric pain and any adverse event—gastrointestinal upset, dry mouth, nausea, vomiting, diarrhoea, rash, and fatigue and its severity using a daily symptom diary and present this for recording at their next clinic visit. At every follow-up visit, a newly filled dispensing sachet containing the experimental drugs with the same numeric code will be given to each woman, and the pills remaining in used sachets are then counted to assess adherence. Adherence will be defined as the use of at least 70% of the prescribed tablets for each participant. Allocations to treatment arms will be concealed from the study investigators, clinic staff, and trial statistician using sealed opaque envelopes that are sequentially numbered. The onsite pharmacy technicians will not be involved in the design, conduct, statistical analysis, and reporting of study findings. Additional information to be collected during the follow-up visits includes a history of allergies, level of treatment adherence, drug tolerability, bedside urinalysis for albumin, venous blood samples for biweekly measurements of haemoglobin, creatinine, liver enzymes (AST/ALT), and complete blood count. Serum biochemical assessments of glutathione and homocysteine levels will be performed at randomisation (baseline) and at weeks 28 and 32. Fetal growth scans and umbilical artery velocimetry (from 32 weeks) will also be done biweekly until delivery. At delivery, data on gestational age (in weeks), total duration of experimental drug intake (in days), intrauterine growth restriction (IUGR), neonatal birth weight (in grams), neonatal status at birth, 7th- and 28th-day (dead/alive), neonatal intensive care unit (NICU) admission, and length of NICU admission (in days) will be collected and recorded in the electronic CRF. Cord blood sampling at delivery for analysis of glutathione and homocysteine levels will also be collected to provide additional insight into maternal-fetal antioxidant transfer and potential downstream effects of NAC [Table 1].

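### The primary endpoint is timed from diagnosis rather than randomisation, so any gap between the two adds untreated days to the reported times; little effect on the comparison between arms is expected

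*Protocol article*

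**What the plan says.** Study outcomes sets the clock for the primary endpoint: time to progression, in days, is "defined as the interval from diagnosis to the first occurrence of a composite endpoint indicating clinical deterioration". On the other end, "Participants who do not experience disease progression will be censored at delivery or at the end of follow-up".

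Three other places work from randomisation:

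- Study population and eligibility criteria excludes "women with preeclampsia with severe features or eclampsia at the time of randomisation".
- The follow-up evaluations text states: "Data collection will commence on the day the participant is randomized into the trial".
- Table 1 has a screening column before the column in which randomisation takes place.

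Two places write the dates as one. The Methods part of the abstract has the tablets taken "in addition to standard antenatal care from diagnosis (randomisation) until either" 34 weeks or delivery, and Randomization and allocation concealment repeats this ("standard antenatal care from diagnosis (randomisation) until either").

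Study procedures starts from women who already have the diagnosis. It continues "Once the study intent and procedures are introduced and informed consent obtained", after which baseline information, blood tests and an ultrasound scan are obtained. No section gives a maximum or expected interval from diagnosis to randomisation.

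**The concern.** In a randomised comparison, time zero is normally the moment of randomisation, because that is when eligibility is fixed and the arms begin to differ. Here the clock may start earlier. Between diagnosis and randomisation a woman takes no study tablet, and if she develops severe features she cannot be enrolled. Time in that interval is therefore free of those events by construction, and the article describes no delayed entry that would remove it from the risk sets.

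The endpoint is stated in days and the Kaplan-Meier curves are a main output, so the absolute times are what readers will see. If the gap is more than trivial, those times describe something other than time since the start of the randomised comparison. Two analysts could also produce different primary outcomes from the same data, one following the outcome definition and the other following the wording that equates the dates.

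**Working it through.** **1. Do the sections fix one origin?** The outcome definition says diagnosis. Eligibility and data collection work from randomisation. The abstract and the randomisation section treat the two as the same date. They would coincide if every woman were randomised on the day of diagnosis, but no section requires that, and consent, blood tests and a scan are described for women already diagnosed. The origin is therefore stated inconsistently.

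**2. What can happen in the gap?** Severe features and eclampsia are exclusions at randomisation, so those events cannot fall in the gap of an enrolled woman. The composite in Study outcomes is wider. It also counts 3+ proteinuria, fetal growth restriction and oligohydramnios, which are neither in the Introduction's list of severe features nor named as exclusions. Counted from diagnosis, such an event could be dated before randomisation and still qualify.

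**3. Effect on reported times.** The article gives no gap length and no time course, so both are assumed. Take 33.3% placebo progression (Sample size calculation) spread over an assumed 42 days at constant hazard: λ = −ln(2/3)/42 = 0.00965 per day. For NAC use λ/2 (the design hazard ratio of 0.5). Let the gap be uniform on 0 to G days. The proportion shown as progressed by day t from diagnosis is (1/G) ∫ [1 − exp(−λ(t − u))] du, for u from 0 to min(G, t). At t = 14:

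| Maximum gap G (days) | Placebo | NAC | Difference (points) | Ratio |
|---|---|---|---|---|
| 0 | 12.6% | 6.5% | 6.1 | 1.93 |
| 7 | 9.6% | 4.9% | 4.7 | 1.95 |
| 14 | 6.5% | 3.3% | 3.2 | 1.96 |
| 28 | 3.2% | 1.6–1.7% | 1.6 | 1.96 |

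The first row equals 1 − exp(−14λ). The absolute figures fall as the gap grows, while the ratio between arms hardly moves.

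**4. Effect on the planned comparison.** The planned analysis is a log-rank test and a Cox hazard ratio, so these were checked by simulation:

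- 130 evaluable women (153 × 0.85), 65 per arm.
- Follow-up from randomisation uniform on 7 to 70 days (assumed; mean 38.5).
- Placebo hazard −ln(1 − 0.333)/38.5 = 0.0105 per day.
- Exponential gap, independent of arm, with the mean shown (assumed).
- 4,000 trials per row. The hazard ratio is the one-step log-rank estimate exp(U/V), averaged on the log scale.

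Each cell gives the result from randomisation / from diagnosis.

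| Mean gap (days) | Type I error (true HR 1) | HR (true 0.5) | Power (true HR 0.5) | Mean recorded days (true HR 0.5) |
|---|---|---|---|---|
| 0 | 0.052 / 0.052 | 0.511 / 0.511 | 0.470 / 0.470 | 32.3 / 32.3 |
| 1 | 0.046 / 0.047 | 0.506 / 0.506 | 0.486 / 0.482 | 32.3 / 33.3 |
| 3 | 0.050 / 0.051 | 0.500 / 0.500 | 0.500 / 0.498 | 32.3 / 35.3 |
| 7 | 0.050 / 0.054 | 0.500 / 0.502 | 0.500 / 0.491 | 32.3 / 39.3 |
| 14 | 0.050 / 0.054 | 0.498 / 0.505 | 0.507 / 0.488 | 32.3 / 46.3 |

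The Monte Carlo standard error is about √(0.05 × 0.95/4000) = 0.003 for type I error and √(0.25/4000) = 0.008 for power. Power is near 0.5 under either origin because of the number of events that these inputs yield; that is separate from the choice of time zero. The recorded time rises by exactly the mean gap.

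**The case against.** The strongest reply is that the article itself equates the dates, in the abstract and in the randomisation section, and that the endpoint is in whole days. If women are randomised on the day of diagnosis the gap is zero and nothing changes. The repeat pressure and urine measurements and the 24-hour collection do not create a gap, because they are part of establishing the diagnosis. A condensed article may also leave enrolment timing to the operating procedures that it says will be developed. All of this stands as far as it goes: the article does not show that a gap of any given length will occur. It does not remove the inconsistency, because the operative definition names diagnosis and nothing obliges same-day randomisation.

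A reader might infer three stronger claims, none of which the documents support:

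- **Every woman contributes untreated time.** No section says that all women are randomised after the day of diagnosis. The point applies only to those who are.
- **Nobody can have an event before randomisation.** This holds for the excluded severe features, but not for 3+ proteinuria, growth restriction or oligohydramnios.
- **This is immortal-time bias in favour of NAC.** The classic bias arises when guaranteed event-free time is credited to one arm. Here the gap precedes randomisation and is balanced in expectation. Chance imbalance in it is ordinary baseline variation, and the simulation shows no material inflation of type I error.

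The fall in the day-14 difference in the working is real, but it is not the planned effect measure.

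**Conclusion.** The time origin of the primary endpoint is badly fixed and should be reconciled. For women not randomised on the day of diagnosis, days to progression are overstated by the length of the gap, the Kaplan-Meier curves move to the right, risk sets mix women at different times on treatment, and a few components could be dated before randomisation.

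No systematic bias between arms is expected. At an assumed mean gap of 14 days the hazard ratio differs by 0.007 (0.505 − 0.498), type I error stays close to 0.05 and power falls by about 0.02 (0.507 to 0.488). These sizes rest on constant hazards, a gap unrelated to arm or risk, and assumed gap and follow-up lengths. The simulation dated all events after randomisation, so it does not cover components dated earlier. The effect is nil if the gap is zero. This is a free improvement to the definition and to the reported times, not a threat to the validity of the comparison.

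**What to change.** Define the primary endpoint as days from randomisation to the first progression event occurring after randomisation. Bring the abstract, Study outcomes, Randomization and allocation concealment, and the follow-up text to that one origin. Record days from diagnosis to randomisation as a baseline descriptor. If diagnosis is kept as the origin for a stated reason, let each woman enter the risk set at randomisation (delayed entry) in both the Kaplan-Meier and Cox analyses.

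The cost is one sentence in the outcome definition, matching edits where the two dates are equated, and one date field for diagnosis if the case report form lacks it. Data collection already starts on the day of randomisation. Eligibility and the required number of events do not change. At submission recruitment had not begun, so the change could be made before any data exist.

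The fix does not need a new check at randomisation that every composite component is absent. Such a check would alter eligibility and is a separate decision.

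### The urine component of the primary endpoint matches neither the entry rule nor the listed assessments: 3+ has no stated confirmation, and the protein/creatinine ratio is not among the listed tests

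*Protocol article*

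**What the plan says.** All references are to the protocol article.

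- **Endpoint (Study outcomes).** The composite works on a first-event, any-component basis: "Disease progression is defined as the development of any of the following". The urine component is "severe proteinuria of 3+ or a urine protein/creatinine ratio of 0.3 or higher". It carries no repeat sample and no interval. The blood pressure component in the same sentence does carry a persistence term: "consistently elevated blood pressure of 160/110 mmHg or higher".
- **Entry (Study population and eligibility criteria).** There are two routes. One is "proteinuria, defined as ≥300 mg in a 24-hour urine collection". The other is a random-sample concentration, "equivalent to ≥2+ on dipstick urinalysis) in at least two random urine samples taken 4–6 hours apart". The second route needs two samples and gives a lower limit only.
- **Baseline tests (Study procedures).** The list is "laboratory (haemoglobin, liver function tests, kidney function tests, glutathione, and homocysteine status". It names no urine protein/creatinine ratio.
- **Follow-up tests (Follow-up evaluations).** The list is "bedside urinalysis for albumin, venous blood samples for biweekly measurements of haemoglobin, creatinine, liver enzymes (AST/ALT), and complete blood count". Its only urine test is the bedside albumin test.
- **Schedule (Table 1).** The laboratory row covers blood count, renal and liver function. The table has no urine row of any kind.

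**The concern.** Entry, endpoint and schedule treat the same measurement in three different ways. The entry rule for random samples accepts that one reading is not enough, and the blood pressure component accepts that one high value is not enough. The urine event, as printed, has neither safeguard, although any single component ends the time-to-event clock.

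A bedside strip is graded in steps, so a chance high reading in a stable woman can become a primary event. The chance of at least one such reading grows with the number of visits. With participants and assessors blinded, these events should fall equally on both arms. They would add the same hazard to each arm and shrink the apparent treatment effect. A woman who already reads 3+ at entry has no progression left to observe on this component.

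The ratio raises a different question. If it is not measured in every woman at the same times, whether and when that limb fires may differ between women for reasons other than disease.

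**Working it through.** **Step 1: set the passages side by side.**

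| | Entry | Primary event | Listed assessments |
|---|---|---|---|
| Strip grade | at least 2+, no upper limit | 3+ | bedside albumin test at follow-up visits |
| Confirmation | two samples, 4–6 hours apart | none stated | none stated |
| 24-hour protein | at least 300 mg (alternative route) | not used | not listed for follow-up |
| Protein/creatinine ratio | not used | 0.3 or higher | not listed at baseline, at follow-up or in Table 1 |

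Three consequences follow:

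- A woman entering at exactly 2+ is one grade from an event.
- A woman entering at 3+ satisfies the dipstick entry rule and may already meet this component. The exclusion of severe features at randomisation does not clearly remove her, because the Introduction's list of severe features does not include proteinuria.
- A woman entering by 24-hour collection need have no strip grade at baseline, so a change in grade cannot be judged for her.

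**Step 2: count the readings.** Visits are two-weekly to 32 weeks and weekly after that. Entry at 24 weeks gives visits at 26, 28, 30, 32, 33 and 34 weeks, which is six up to 34 weeks. Entry at 30 weeks gives 32, 33 and 34, which is three. Later entry gives fewer; readings continued to delivery give more.

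**Step 3: illustrate the accumulation.** The article gives no false-reading rate. Assume a stable woman has probability p per visit of a false 3+, independent across visits. Over k visits the chance of at least one is 1 − (1 − p)^k.

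| p (assumed) | k = 3 | k = 6 |
|---|---|---|
| 2% | 1 − 0.98³ = 5.9% | 1 − 0.98⁶ = 11.4% |
| 5% | 1 − 0.95³ = 14.3% | 1 − 0.95⁶ = 26.5% |
| 10% | 1 − 0.90³ = 27.1% | 1 − 0.90⁶ = 46.9% |

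**Step 4: illustrate the dilution.** Take the sample-size inputs: 33.3% progression on control and a hazard ratio of 0.5. Treat both as describing true progression over the same visits. The control cumulative hazard is H = −ln(1 − 1/3) = 0.4055. False readings add h = −k·ln(1 − p) to both arms. The apparent hazard ratio is (0.5H + h)/(H + h).

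| p (assumed) | k = 3: h, apparent HR | k = 6: h, apparent HR |
|---|---|---|
| 2% | 0.0606, 0.57 | 0.1212, 0.62 |
| 5% | 0.1539, 0.64 | 0.3078, 0.72 |
| 10% | 0.3161, 0.72 | 0.6322, 0.80 |

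For example, with p = 5% and k = 6: (0.2027 + 0.3078)/(0.4055 + 0.3078) = 0.5105/0.7133 = 0.72.

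The additional events do not compensate. Take 153 × 0.85 = 130 evaluable women and the usual log-rank approximation, power = Φ(√events × |ln HR|/2 − 1.96). Without false readings there are about 33.6 events and power is about 52%. With p = 5% and k = 6 there are about 59.1 events, but power at the apparent 0.72 is about 25%. That the starting value is below the planned 80% is a separate sample-size matter and is not argued here.

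**Step 5: effect of confirmation.** If the second strip were independent of the first, the per-visit false rate would fall to p², giving 1 − (1 − p²)^6 = 0.2%, 1.5% and 5.9% over six visits. Two strips from the same woman a few hours apart are unlikely to be fully independent, so these are best-case figures.

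**The case against.** The strongest reply is that a journal article condenses the full protocol, and that silence on confirmation is not a rule that one reading suffices. Platelets, creatinine and liver enzymes also carry no repeat rule, and operating procedures for data collection and follow-up are promised under Ethical considerations. Part of this stands: a confirmation rule may exist elsewhere. But what counts as an event is fixed by the printed definition. The article states confirmation for random-sample entry and persistence for blood pressure, and it leaves the urine event without either.

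A reader might infer that the ratio is never measured, or only when a clinician chooses to order it. The documents do not support that. The follow-up list is introduced as what is included, not as exhaustive. Table 1 omits even the urinalysis that the text schedules, so absence from the table is weak evidence. What can be said is that uniform measurement is not shown.

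A reader might also infer that every woman starts one grade from an event. That holds only for entry at exactly 2+.

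A reader might take 47% as an estimate of false events. It is not one. The rates are assumed, independence within a woman is assumed, and six visits requires entry at the start of the window.

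Finally, under blinding the noise should be non-differential. It weakens the trial but is not a route to a false claim of benefit. That stands and limits the weight of the point.

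**Conclusion.** The point holds as a mismatch between entry rule, endpoint definition and listed assessments, and it is worth correcting before enrolment. The textual part needs no assumption: 3+ has no stated confirmation, dipstick entry has no upper limit, and the ratio is in the endpoint but in none of the listed assessments.

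The direction of the effect, towards a hazard ratio of 1 with lost power, rests on blinding being maintained. Its size is unknown. The percentages and apparent hazard ratios above depend wholly on assumed rates of 2–10% per visit, independent readings, and every woman being at risk of a false 3+. They show a mechanism, not an expected loss. The comparison with 33.3% also depends on how the cited source defined progression, which cannot be seen here. Whether 0.3 is the right ratio threshold is a separate question and is not part of this point.

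**What to change.** These changes concern endpoint ascertainment only, not clinical management.

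1. Count 3+ proteinuria as a primary event when it is present in at least two samples taken 4–6 hours apart (the protocol's own rule for random-sample entry), in women below 3+ at randomisation. Date the event at the first of the two samples.
2. Record a strip grade at randomisation in every woman, including those who enter by 24-hour collection, so that rule 1 can be applied. Women at 3+ at randomisation then contribute through the other components.
3. Reconcile the ratio with the schedule: either remove it from the primary event, or measure it at baseline and at every visit in all women. Which of the two is the investigators' choice.
4. Add a urine row to Table 1 that matches whatever is decided.

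The cost is endpoint wording, a baseline strip where none exists, a same-day repeat strip for women who read 3+, and slightly fewer counted events. Keeping the ratio would add a laboratory test at each visit. The article states that recruitment had not begun at submission, so a change made before the first enrolment would affect no data already collected.
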